**F. Estimated study mortality**

Using statistics from Chris Hani Baragwanath Hospital, 50% (450) of the HIV-infected children enrolled in the study will die within the first year of life. The infant mortality rate for children between 6 weeks and 2 years of age in Soweto is approximately 10/1000, suggesting that an additional 220 children will also die during one year of follow-up. In total, an estimated 670 children in the study cohort will die per annum.

**G. Interim analysis**

No formal interim analysis of the efficacy data is planned and no early termination of the study due to early evidence of efficacy is planned. Once 28 outcome cases have been accrued, enrolment into the study will stop. The International Advisory Committee (Section XIII.A) will then meet to discuss whether/how long surveillance for outcome cases should continue. Follow-up will likely occur until 43 cases have been accrued. Quarterly reports of safety data, including adverse events and deaths, and reports of cases of pneumococcal disease and pneumonia will be reviewed by the Safety Monitoring Committee (SMC). Conditional power calculations or the probability of ever showing significant efficacy given the observed number of outcome cases in each vaccine group and an assumed level of vaccine efficacy, may be provided if requested by the SMC. The study could be terminated early only if one of the following is concluded by the SMC:

(1) significant safety concern

(2) increased pneumococcal disease risk in the vaccinated group, or

(3) extreme low probability of demonstrating efficacy even if the study is carried through to the end

**X. Adverse reactions**

The results of the Phase II trial assessing the safety and immunogenicity of the nonavalent pneumococcal conjugate vaccine, which is presently being concluded at Zola clinic, will be available soon. Preliminary data from 500 children suggest the vaccine to be well-tolerated. No serious adverse reactions were recorded. During the proposed efficacy study all children will be monitored for 15 minutes after vaccination for any signs or symptoms of adverse reactions. Resuscitation facilities will be available at all the health centers. All signs or symptoms will be recorded on an Adverse Reaction Form as well as on the Road to Health card.

Parents will also be advised to watch for signs and symptoms of local reactions, including erythema, swelling, induration and/or tenderness at the site of vaccination and for systemic reactions, such as difficulty with breathing, drowsiness, vomiting and fever lasting for greater than 24 hours. Parents will be instructed to bring their children to the clinic/hospital immediately for medical assessment and/or management for any vaccine event of concern.

Parents/guardians will be asked to request doctors/nurses not directly involved with the study to note any event requiring medical attendance on their Road to Health card, including the clinical diagnosis and treatment given. The Road to Health card, which is usually safeguarded by the parent/guardian, will be reviewed at each vaccination visit. The card will also be reviewed by the admitting physician should the child require hospitalization.

Any patient experiencing a serious clinical adverse reaction will have a detailed history, physical examination and appropriate laboratory procedures done by a study pediatrician. All deaths, life-threatening events, and all unexpected vaccine-related events will also be investigated. These events will be reported to the Safety Monitoring Committee and WLVP monthly.

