**V. Trial design**

**A. Enrolment**

All children presenting to immunization clinics in Soweto or Orange Farm [Appendix 3] for routine immunization at approximately 6 weeks of age will be evaluated for study participation. Children will qualify for enrolment by meeting all inclusion criteria and none of the exclusion criteria, as determined by obtaining a medical history and performing a physical examination prior to immunization. The parent/guardian must also give consent for the child to participate in the study. Staff hired specifically for the study will do recruitment, immunization (study and routine vaccines), and follow-up.

The annual birth cohort in Soweto is approximately 24,000. It is anticipated that the entire birth cohort over a two-year period will be recruited.

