**D**. **Treatment period**

Each study subject will receive three injections of either pneumococcal conjugate vaccine or placebo, administered concurrently with TETRAMUNE®, OPV, and Hep B. The injections will be administered at approximately 6, 10, and 14 weeks of age, with a minimum interval of 3 weeks between each dose and all three doses must be completed by 9 months of age. Children not returning within 1 week of the appointed time for the second or third vaccinations will either be telephoned or visited at home.

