**F. Follow-up**

**1. Vaccine Safety**

Following each vaccination, the child will be monitored at the clinic for approximately 15 minutes for any immediate local and/or systemic reactions. The parent/guardian will also be asked to observe for untoward effects which might occur within one week of vaccination. If the parent/guardian has concern, they will be asked to report these reactions to the study nurse as soon as possible. Any child with a clinical event of concern to the parents will be evaluated by the study nurse or other medical personnel. In the event that the child is hospitalized, the parent will be asked to contact the investigator immediately. Study pediatricians will also be conducting daily surveillance for hospitalization of study participants. Participation in the vaccine study will be noted on the child’s Road to Health card, which is presented at hospital visits.

All efforts will be made to obtain follow-up information on deaths which occur outside of the hospital through death notifications, cemetary records, etc..

The frequency of adverse events following vaccination will be assessed for both the placebo and treatment groups.

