**C. Immunogenicity study**

A list of children to participate in the immunogenicity study will be generated by WLVP and will include subjects who have received either the conjugate vaccine or placeboat any one of the study sites. One nurse will be specifically responsible for obtaining blood specimens from the appropriate children; therefore, for logistical reasons, only children who have received all 3 doses of the vaccine/placebo at the same clinic will be eligible for the immunogenicity study. As there is no scheduled clinic visit at 18 weeks, the informed consent will be given to the parents at the 14 week visit. To ensure that blood is taken from appropriate numbers of children given either placebo or conjugate vaccine, the study identification numbers of children initially randomized into the immunization study who, for any reason, are not bled, will be sent to WLVP. A list of alternate children will then be generated.

Approximately 2 ml of blood will be taken by finger stick at 18 weeks, 4 weeks after the third immunization. The blood will be collected in a red tube and then the sera will be removed after clotting and centrifugation and stored at -70oC.

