**D. Assessment of vaccine safety**

1. All children will be observed for 15 minutes following vaccine administration for any immediate local and/or systemic reactions at the clinic by qualified study personnel. Parents will also be advised to return to the clinic immediately should the child develop reactions of concern to the parent. Follow-up will occur on all allergic reactions, severe local reactions within 72 hours of vaccination, as well as on all seizures occurring within 4 weeks of vaccination.

2. The study pediatricians will conduct daily surveillance for hospitalization of study children (see Section VIII) at Chris Hani Baragwanath Hospital. All deaths, life-threatening events, and unexpected events related to the vaccine will also be investigated. Efforts will also be made to follow-up all deaths occurring outside of the hospital through death notifications and cemetery records. Prior to implementation of the study, meetings will be held with the pediatricians of the hospitals to inform them of the nature of the study and the need to notify study investigators should they see study participants. Reminder notices will be placed in the appropriate wards and the children’s Road to Health cards will also be clearly labelled so as to indicate their participation in the study. The majority of mothers bring the Road to Health card when the child is hospitalized.

3. The Safety Monitoring Committee (see Section XIV) and WLVP will review safety data quarterly during the trial. All severe, life-threatening reactions or the deaths of study participants, regardless of the etiology, and unexpected events felt by the study physicians to be vaccine-related will be reported monthly to the members of the Committee as well as to WLVP. Quarterly reporting to WLVP will include all of the above reactions as well as seizures or changes in neurological status within one month of vaccination and severe local or systemic reactions or allergic reactions within 72 hours of vaccination. A report of the incident cases of pneumococcal disease will be provided to the Safety Committee quarterly.

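### The protocol promises follow-up of all seizures within 4 weeks of each dose, but parents are asked to watch for one week only, and no scheduled contact closes the window after dose 3

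*Protocol*

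**What the plan says.** **The commitment.** Protocol VI.D.1 provides for follow-up of allergic reactions, of severe local reactions within 72 hours, "as well as on all seizures occurring within 4 weeks of vaccination". VI.D.3 adds that quarterly reporting to the sponsor includes "seizures or changes in neurological status within one month of vaccination".

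**What parents are asked to do.** V.F.1: "The parent/guardian will also be asked to observe for untoward effects which might occur within one week of vaccination". Section X lists signs to look for: local reactions and, as examples of systemic reactions, breathing difficulty, drowsiness, vomiting and prolonged fever. Seizures are not named. Sections VI.D.1 and X also tell parents to come back for anything that concerns them.

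**The card.** Under X, parents ask outside doctors and nurses to "note any event requiring medical attendance on their Road to Health card, including the clinical diagnosis and treatment given". X continues: "The Road to Health card, which is usually safeguarded by the parent/guardian, will be reviewed at each vaccination visit". The admitting physician also reviews it if the child is hospitalised.

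**The visits.** V.D: "The injections will be administered at approximately 6, 10, and 14 weeks of age, with a minimum interval of 3 weeks between each dose". VI.C explains why consent for the blood sample is handed out at 14 weeks: "As there is no scheduled clinic visit at 18 weeks". The schedule table in VI.B.3 then shows routine vaccination visits at 9 and 18 months.

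**The concern.** The protocol sets a 4-week window for seizures but gives parents an instruction that ends after one week. After doses 1 and 2 a study visit brings the child back at about the end of the window. There is a medical assessment before the next dose (VI.B.1), a card review (X), and a telephone call or home visit for children who do not attend (V.D, VI.B.4). After dose 3 none of this is scheduled.

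At stake is the count of non-hospitalised seizures. These feed the between-arm comparison of adverse-reaction report rates by Fisher's exact test (IX.C.5) and the quarterly safety reports (VI.D.3, XII.A). Seizures within 4 weeks are an event that the protocol itself singles out, so the means of finding them should match the commitment.

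**Working it through.** The protocol gives no figure for how many doses are covered by a later check, so there is none to reproduce. The steps below compare windows and count doses.

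**1. Parent watch against seizure window.** Watch: 7 days (V.F.1). Window: 28 days (VI.D.1). Days outside the watch: 28 − 7 = 21, that is days 8 to 28, after every dose.

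**2. What later study visits cover.** Count the weeks of each 4-week window that have passed by the time of a later study visit.

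| Spacing | Dose 1 | Dose 2 | Dose 3 | Total |
|---|---|---|---|---|
| 4 weeks between doses | 4 | 4 | 0 | 8 of 12 (67%) |
| 3 weeks between doses (permitted minimum) | 4 | 3 | 0 | 7 of 12 (58%) |

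At 3-week spacing the dose-1 window is still completed by the dose-3 visit, 6 weeks after dose 1. The dose-2 window is covered only to day 21. The gap is therefore largest after dose 3 but not confined to it.

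**3. Share of doses with no later study visit.** The expected cohort is about 48,000 (Protocol Summary).
- All children complete: 48,000 / (48,000 × 3) = 48,000 / 144,000 = 33.3%.
- 98% complete three doses, the Phase II figure in III: each child has one last dose, so the share is 1 / (0.98 × 3 + 0.02 × m), where m is the number of doses that the other 2% receive. This is 33.8% for m = 1 and 33.6% for m = 2.
- Leaving out the 400 children bled at 18 weeks (IX.C.4): (48,000 − 400) / 144,000 = 33.1%.

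**4. Timing of the next listed vaccination visit.** Nine months is 9 × 365.25 / 12 / 7 = 39.1 weeks.
- With dose 3 at 14 weeks, the visit is 39.1 − 14 = 25.1 weeks after the dose.
- The window closes at 18 weeks of age, so the visit is 39.1 − 18 = 21.1 weeks after that. This is longer than one quarterly reporting period of about 13 weeks.

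**The case against.** The strongest reply is that the protocol may already contain the missing check. Section X speaks of every vaccination visit, not only study-vaccine visits. The schedule table has a visit at 9 months, and V.A says: "Staff hired specifically for the study will do recruitment, immunization (study and routine vaccines), and follow-up". On that reading a card entry made after dose 3 would be read by study staff. This stands as a possible reading. However, no section says that study staff read the card or complete an Adverse Reaction Form at 9 months, and that visit comes about 21 weeks after the window closes.

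A reader might infer that events after dose 3 have no route of capture at all. The documents do not support this. After every dose the child is observed for 15 minutes, parents can report to the nurse or return to the clinic with no time limit on that advice, hospital admissions are under daily surveillance, and the admitting physician reviews the card. Capture after dose 3 is passive and weaker, not absent.

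A reader might also extend the point to allergic and severe local reactions. The 72-hour period in VI.D lies wholly inside the one-week watch, so the mismatch concerns seizures only.

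Finally, it is tempting to turn one third of doses into a share of events lost, or to argue that dose 3 is where sensitisation would appear. The first needs detection rates for parent report and card review, and the protocol gives neither. Nothing in the protocol supports the second.

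**Conclusion.** The point holds in a limited form. The one-week parent watch and the list of signs do not match the 4-week seizure commitment for any dose. Study visits partly make up for this after doses 1 and 2. After dose 3, about one third of doses, no scheduled contact falls within or at the end of the window outside the immunogenicity subset. Non-hospitalised seizures on days 8 to 28 then rest on unprompted parent report, or on a late card review that is not clearly assigned.

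Allocation is randomised and blinded, so under-counting should be similar in the two arms. The likely effects are fewer counted events, some loss of power in the safety comparison, and late reporting to the Safety Monitoring Committee. Bias toward one arm is not to be expected. The one-third share assumes that nearly all children complete three doses. The number of seizures missed cannot be derived from the documents.

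**What to change.** - In V.F.1 and X, name seizures among the events to watch for, and ask parents to report them for 4 weeks after each dose, in line with VI.D.1. This does most of the work, because it acts within the window and covers all three doses.
- In X, state that the card review includes the existing 9-month visit or the next clinic contact after dose 3. There, study staff read the card, ask about seizures within 4 weeks of dose 3, and complete an Adverse Reaction Form for any that are found. The alternative contact is needed because V.D lets dose 3 be given as late as 9 months, when the measles visit could coincide with it.

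The cost is a few more parent reports to handle, and a card check with a form entry at a visit already in the schedule. The 9-month check is only a late backstop: it comes about 21 weeks after the window closes for a child given dose 3 at 14 weeks, with some recall error where the card has no entry.

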**XI. Data management and data quality control**

Each Vaccination Report form will be reviewed and initialed by the study nurse. Once reviewed by the clinical monitors, the forms will be brought to SAIMR for entry into a SAS computer program. Data from the Vaccination Report forms, the Adverse Reactions forms, the Clinical Outcome forms, and Laboratory forms will be entered onto desk-top computers and verified using appropriate range checks. The data will be entered within one week of collection so that an up-to-date list of study participants is available to the study pediatricians for surveillance of outcome cases. Data files containing only the necessary variables for identification of study participants will be created for both the hospital surveillance and for questions from clinic nurses. Individual data entry clerks will be assigned specific clinics whose data they will enter and to whom they will send a weekly listing of those patients, initially randomized at their clinic, who were vaccinated the previous week at any study site; the study nurses will also be given a list of those patients who failed to return for scheduled visits. They will also be responsible for contacting the study nurses to resolve data queries.

Data from each data entry clerk will be backed up daily; the master file containing the data from all of the clinics will be updated and backed up weekly.

**XII. Study monitoring**

Monitoring will be the responsibility of the SAIMR investigators and WLVP and their local representatives. Independent local monitors hired by WLVP will perform primary monitoring of the study sites. Safety monitoring will be the responsibility of the Safety Monitoring Committee.

**A. Safety**

Vaccine safety will be monitored and reported as described in Section XI. Safety will be analyzed as the trial progresses, with reports on adverse reactions and outcome cases provided to the Safety Monitoring Committee on a quarterly basis. Deaths, life-threatening events, and unexpected events judged to be vaccine-related will be reported to the Committee monthly. All serious adverse events will be investigated.

**B. Progress of the Study**

A summary of the progress of the trial will be provided by the investigators to WLVP on a monthly basis and to the International Advisory Committee and the Safety Monitoring Committee on a quarterly basis.

**C. Verification of Data**

Study investigators from SAIMR and WLVP monitors will monitor the participating clinics. Monitoring visits will occur before the study begins, at regular intervals during the trial, and at the completion of the trial. Monitoring will be conducted to:

1. Assure that the Informed Consents are properly signed and dated. It is anticipated that a random sample of 20-25% of informed consents will be monitored.

2. Assure adherence to the protocol.

3. Audit and review data derived from and pertinent to the study for accuracy and completeness of information. This includes Vaccination Report forms, subject medical records, laboratory reports, etc. Approximately 20-25% of report forms will be randomly monitored.

4. Personnel from SAIMR will examine records for accurate documentation of quantity and date of receipt of investigational vaccine, dispensation and accountability data regarding administration to each study participant, loss of investigational materials, and unused supplies.

5. Review Investigator files for required documents, e.g. IRB protocol approvals, protocol amendments, and informed consents.

6. Prepare monitoring reports that record and report observations on the progress of the trial, continued acceptability of the facilities, and fulfillment of obligations by the Investigator.

**XIII. Study advisory committees**

Two independent advisory committees have been established to assist in the design, on-going implementation, and interpretation of study results.

**A. International Advisory Committee (IAC)**

An International Advisory Committee has been established whose role is as an advisory body to make recommendations to the Principal Investigator and the manufacturer.

The specific roles/responsibilities of the committee are as follows:

1. The IAC will provide technical advice and oversight on protocol development; on data collection, management, and analysis; and on ways to improve the conduct of the trial, if any are identified, during the trial. The IAC will review data and advice from the Safety Monitoring Committee, progress reports from the Principal Investigator, and reports from any site visitors or consultants. The IAC will have the authority to recommend the trial be stopped, if it concludes, on the basis of information provided to it, that the vaccine is unsafe or that for other reasons it would be unethical to continue. The IAC may also recommend the trial be extended, if additional enrollment and surveillance would increase the statistical power of the study.

2. Membership of the IAC will consist of individuals, none of whom have any formal connection with the vaccine manufacturer WLVP. Individuals for the Committee were chosen based on their expertise in the field of acute respiratory infections in children or in the conduct of clinical trials such as the one proposed. The Committee will comprise:

[name]

US Centers for Disease Control and Prevention

[name] (Chairman)

Division of Child Health and Development

The Johns Hopkins University

[name]

ARI Programme

World Health Organization

[name]

District Health Care Services

City Health Department

Greater Germiston Transitional Metropolitan Council

[name]

Biometry Section

US National Institute of Allergy and Infectious Diseases

3. The Principal Investigator will actively participate in IAC meetings, while participants from WLVP will have observer status. The Committee also has the option of holding some meetings in closed session. Both the Principal Investigator and WLVP participants will receive copies of all Committee documents.

4. The World Health Organization will provide support and serve as a focal point for communication among the committees, WLVP, and the Principal Investigator. The secretariat will provide summaries of the discussions and recommendations of each IAC and Safety Monitoring Committee meeting and will coordinate the planning for these meetings.

5. The IAC will meet at least once a year or more frequently, if requested by the Chairperson, to review the trial progress and consider information or advice provided by the Safety Monitoring Committee. The IAC and the Safety Monitoring Committee should schedule some meetings concurrently to facilitate interaction and discussion between the two committees.

